## Abstract

**Background:**

Many studies have shown the effectiveness of self-management for patients with asthma. In particular, possession and use of a written asthma action plan provided by a doctor has shown to significantly improve patients’ asthma control. Yet, uptake of a written asthma action plan and preventative asthma management is low in the community, especially amongst adults.

**Objective:**

A Web-based personally controlled health management system (PCHMS) called Healthy.me will be evaluated in a 2010 CONSORT-compliant 2-group (static websites verse PCHMS) parallel randomized controlled trial (RCT) (allocation ratio 1:1).

**Methods:**

The PCHMS integrates an untethered personal health record with consumer care pathways and social forums. After eligibility assessment, a sample of 300 adult patients with moderate persistent asthma will be randomly assigned to one of these arms. After 12 months of using either Healthy.me or information websites (usual care arm), a post-study assessment will be conducted.

**Results:**

The primary outcome measure is possession of or revision of an asthma action plan during the study. Secondary outcome measures include: (1) adherence to the asthma action plan, (2) rate of planned and unplanned visits to healthcare providers for asthma issues, (3) usage patterns of Healthy.me and attrition rates, (4) asthma control and asthma exacerbation scores, and (5) impact of asthma on life and competing demands, and days lost from work.

**Conclusions:**

This RCT will provide insights into whether access to an online PCHMS will improve uptake of a written asthma action plan and preventative asthma actions.

**Trial Registration:**

Trial Registration: Australian New Zealand Clinical Trials Registry ACTRN12612000716864; https://www.anzctr.org.au/Trial/Registration/TrialReview.aspx?id=362714 (Archived by WebCite at http://www.webcitation.org/6IYBJGRnW).

## Introduction

### Background

Around 300 million people worldwide currently suffer from asthma [1]. The mortality caused by asthma is significant since a global estimation attributes to this disease about 1 in every 250 deaths [1]. Living with asthma is also difficult. People with asthma report worse health and quality of life than those without asthma [2,3].

Solutions have been developed to help people with asthma cope with their condition [4]. One of the key elements to optimal asthma management is to achieve good control of the disease. To achieve that, patients’ knowledge in recognizing asthma symptoms, identifying risk factors, using medication, and managing asthma exacerbations is important. Further, the relationship between patients with asthma and healthcare providers is crucial to develop an efficient asthma self-management plan [5].

One of the most useful tools in facilitating effective asthma self-management is the use of an individualized written asthma action plan, which describes different tailored steps of actions for the patient to follow according to their asthma severity. Written asthma action plans are claimed to be one of the most effective means for asthma self-management in several systematic reviews [6-8]. A Cochrane review by Gibson and colleagues concludes that use of a written asthma action plan, combined with regular visits to the doctor and education about asthma, leads to fewer visits to the emergency department, less hospital admissions, better lung function, and improvement on symptoms [6]. Online social networks and personal health management systems represent an innovative intervention to help patients engage with clinicians, health services, and self-management [9]. Despite strong evidence for the efficacy of written asthma action plans, they are widely under-used. Even after over 20 years of recommendation, only about one in 5 people with asthma have a written asthma action plan [10].

In Australia, the prevalence of asthma is particularly high and represents one of the highest in the world [2,3]. More than 1 in 10 adults and children is estimated to be suffering from asthma, representing more than 2 million Australians [2]. Although prevalence of asthma has declined over the last decade, the mortality caused by this disease remains significant with 411 people reported to have died from asthma in 2009 in Australia. According to a survey from the Australian Council of Asthma Monitoring in 2007 and 2008, only 21.3% of all-age patients with asthma are reported to possess a written asthma action plan [2,3]. This rate dropped to 14.4% when considering a subgroup of people aged 15 years and over [2].

There are a number of explanations for the under-usage of written asthma action plans by patients. Firstly, the diagnosis of asthma may not have been made in primary care where symptoms have been treated, if the disease is not labeled then patients may not be provided with long-term self-management tools [11]. When asthma is properly diagnosed, some health professionals provide patients with oral instruction instead of a formal written asthma action plan [12]. Others may consider asthma action plans as inefficient tools because of a lack of information and a difference of perception of asthma between patients and doctors [13,14]. From the patient’s point-of-view, asthma action plans can also be perceived as irrelevant or be under-used because of a passive attitude toward their asthma. This can prevent them from taking personal control of their asthma [15,16]. Finally, another reason could be that patients do not visit healthcare professionals to obtain or to update their asthma action plan, or do not ask for it when they see their general practitioner [15].

For asthma, Internet-based self-management appears to be a promising approach to improve control of this condition [17-21]. The aim of this study is to test a Web-based personally controlled health management system (PCHMS), in supporting consumers with asthma to encourage the uptake and use of a personal written asthma action plan, and to proactively seek self-management advice and schedule planned general practitioner (GP) visits before experiencing an asthma exacerbation. The PCHMS, called *Healthy.me,* has been previously tested with patients undergoing in-vitro fertilization (IVF) [22], in a randomized controlled trial to improve uptake of influenza vaccination [23,24], and amongst university students about help-seeking behaviors for physical and emotional well-being [25,26].

### Study Aims and Hypotheses

Specific hypotheses to be tested in this study are that:

Consumers using a Web-based PCHMS with interactive and social features are more likely to follow evidence-based guideline recommendations for asthma management, as measured by the rates of obtaining or updating a written asthma action plan with their GP and the usage rates with the asthma action plan, measured by questionnaires;Use of a PCHMS will contribute to improved asthma control and reduced rates of asthma exacerbation compared to those using only static websites (usual care arm).

## Methods

### Study Design

A randomized controlled trial with a 2-group parallel design (with intervention allocation ratio 1:1) will be used to evaluate the efficacy of the Web-based PCHMS *Healthy.me*, reported in accordance to the 2010 CONSORT statements [27](ACTRN12612000716864). The PCHMS is not part of usual care but aims to improve usual care as measured by compliance to evidence-based guidelines.

Participants randomized to the *intervention* group will have immediate access to an interactive version of *Healthy.me* with full PCHMS features as described later, from the date they are recruited.Participants randomized to the *control* group will receive access to a static webpage, without PCHMS features or any interactive component. This webpage will offer links to Australian information websites about asthma.

### Participants

Participants meeting eligibility criteria will be invited to use *Healthy.me* for 12 months. Participants will be assigned to intervention (access to *Healthy.me*) or control (access to static website) by random allocation generated by a computerized random-number generator [28]. Participants may be randomly selected to attend a 1-hour interview (or focus group) to discuss their asthma management and feedback at the end of the study. The participant inclusion eligibility criteria are as follows: (1) aged 18 or above, (2) living in Australia at the time of the study, (3) easy access to the Internet and email on a regular basis, (4) doctor diagnosis of asthma, and (5) adequate English reading and written ability. Participants currently enrolled in other trials of *Healthy.me* are excluded.

#### Recruitment Strategy

The recruitment of participants will be made possible with the assistance of Asthma Foundation Australia, the National Asthma Council Australia, and other consumer groups which have an online presence, to advertise our study using their existing participant engagement methods (ie, electronic newsletters and website). Because the study requires participants who are familiar with the use of the Internet, special emphasis will be given to Internet-based recruitment. Calls for research participants will be made on Google, Facebook, Twitter, and other online/social media on a regular basis, as well as on an online notice board (Gumtree Australia). It will also be possible that some participants will be recruited by others participants (snowballing sampling) via sharing in social networks, and thanks to the “invite a friend” feature they will be able to use on *Healthy.me* website.

Interested participants will be directed to a website with detailed information about the study. All consenting participants (control and intervention) will then be directed to a secure website to complete an eligibility screening survey.

#### Ethical Concerns and Consent

Ethics approval for this study has been obtained from the University of New South Wales (UNSW) Human Research Ethics Committee (approval no. HC12213), and from the National Research and Evaluation Ethics Committee of the Royal Australian College of General Practitioners (RACGP) (approval no. NREEC 12-005). Eligible participants will complete their written consent form online; the revocation of consent form is also available online.

### Intervention and Control

All participant volunteers responding to the invitation are required to register online by providing consent, completing a 3-minute eligibility questionnaire. Those eligible will then be invited to complete a 10-minute online pre-study survey and to watch a 3-minute online tutorial about *Healthy.me*. All eligible participants will also complete a 5-minute monthly survey during the study and a 10-minute post-study survey at 12 months. The control and intervention arms of the trial run concurrently, meaning that the randomly allocated participants of the trial will be exposed to the same environmental condition (eg, season), and the same background of public health campaigns.

#### Description of Intervention

*Healthy.me* consists of the following features:

*Personal Health Record (PHR)*. Allows for self-recording of medical test results and health measurements.
*Pillbox*. Allows for self-recording of current medications and medication adherence.
*Schedule, to-do list, and reminders*. An online schedule to self-record and keep track of health-related appointments, to-do items, which sends email reminders, and allows participants to book appointments with their health service providers.
*Team*. A feature that allows the self-recording of clinical and non-clinical personnel looking after one’s health.
*Journeys*. Consumer-specific care pathways that provide knowledge for health service engagement and self-management in an actionable way. These pathways describe the different stages in the management of health conditions that can be used to personalize other PHR sections in the system, and provides advice on what to expect and how to prepare for each stage (Participants in this study will have access to three asthma management journeys with content developed in collaboration with Asthma Foundation NSW, and adapted from its website [29]).
*Social communication spaces*. Support rich interaction across the continuum of care between participants and clinicians. The features include: (1) a poll system in which participants will be able to answer simple health-related questions and compare their response with other participants’ aggregated and de-identified responses; (2) ability to send and receive email messages with other participants on *Healthy.me*; (3) *diary* which offers a private place (by default but with the possibility to share with other participants) for participants to write down their thoughts and feelings; and (4) forums (moderated by a GP and the research team).
*Online appointment booking service.* This feature allows participants to be directly connected by telephone and at no charge with their health professional after clicking on a button. The 3 steps of the protocol are: First, participant clicks on a “book now” graphic button in *Healthy.me* and confirms his/her telephone number as well as health professional’s one; Second, participant and health professional receive an automatic ongoing call from the service, and Third, participant and health professional are connected each other and can book an appointment over the phone.

#### Intervention Group and Exposure

The period of access to *Healthy.me* will vary depending on the date of participant registration (from 9 to 12 months). During the study *Healthy.me* will provide participants in the intervention group with information and forward email reminders about asthma, indications for managing their asthma or other medical concerns, should they wish to use that service.

The intervention will not modify in any way the standard procedures of healthcare provision by GP clinics.

A pilot study has been conducted with 9 adults including 3 participants with asthma. Issues on system usability, journey content, surveys, study protocol, and advertisement material have been resolved before recruiting participants with asthma to participate in their normal setting.

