### Sample Size

A conservative estimate of at least 300 participants with 150 in each arm is needed to detect a 15% point difference in possession rate of a written asthma action plan between the control group (14.4%) and the intervention group (29.4%). This estimate is calculated at 5% level of significance, 80% power (2-sided test), with an anticipated participant dropout rate approximately 25%.

The effect size estimate is based on previous studies using *Healthy.me* assessing the efficacy of Internet-based interventions on the uptake of preventative health actions [23], and on studies with interventions promoting the use of personal asthma action plans [13]. The base rate is the percentage of adults (ie, 15 years and over) with current asthma in Australia and possessing a written asthma action plan, reported in the Australia Centre for Asthma Monitoring analysis of the Australian Bureau of Statistics National Health Survey 2007-2008, and cited in the Australia Centre for Asthma Monitoring 2011 report [2].

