### Outcome Measures

The primary measure is the number of participants who have obtained, or have updated, their written asthma action plan with a GP within the 12 months of the study. The secondary outcomes concern actual use rate of the written asthma action plan, number of unplanned visit to healthcare for asthma, usage of *Healthy.me*, asthma symptoms, and competing demands on health and asthma. Please see Table 1 below.

**Table 1 table1:** Summary of outcome measures.

Outcome measures		Measurement time points & methods		Time	
			Baseline	Monthly	Completion

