### Study Procedure

Table 3 below summarizes participant procedures in the study. The duration of the study is expected to be 12 months.

Email will be the primary channel to communicate with participants for study information and reminders about survey completion. From the time participants are recruited until study completion, all participants (control and intervention) will receive an email each month to complete a 5-minute survey about their health in the past month. At study completion, all participants will receive an email asking them to complete a post-study survey. In order to ensure the completeness of data collection, there will be 2 follow-up emails sent 5 days apart from each other to remind those who have not completed each survey.

**Table 2 table2:** Surveys used in the study.

Survey	Purpose
Screening survey	Eliciting participants’ eligibility criteria.
Pre-trial survey	To obtain participants’ demographics and experiences of asthma management at study enrolment.
Monthly follow-up questions	To obtain participants’ self-reported symptoms of asthma (ie, asthma control and exacerbation), impact on work and study due to asthma symptoms, and competing demands and health throughout the study.
Post-trial survey (12 months after the beginning of the study)	To obtain participants’ state of asthma control and asthma management. For those who receive the PCHMS version of *Healthy.me*, their perceived usefulness of *Healthy.me* will also be assessed.

**Table 3 table3:** Stages of study procedure.

Stage of study	Procedure

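### Access to Healthy.me is 12 months in some sections and 9 to 12 months in another, and the plan does not fix whether the 12-month outcome window runs from each participant's own start or to a common closing date

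*Protocol article*

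**What the plan says.** All references are to the protocol article.

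**Length of access.** The Abstract has participants assessed after a year of using either Healthy.me or the information websites, and the Participants section invites eligible people to use Healthy.me for a year. Intervention Group and Exposure says instead that access "will vary depending on the date of participant registration (from 9 to 12 months". Study Design starts intervention access on the date of recruitment. The Control section delays control participants' access to the full system by 12 months.

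**Timing of the outcome.** Outcome Measures counts plans obtained or updated with a GP "within the 12 months of the study". Intervention and Control has all eligible participants complete "a 10-minute post-study survey at 12 months". Table 2 lists the "Post-trial survey (12 months after the beginning of the study". Study Procedure expects the study to last 12 months. It sends monthly surveys to both arms from each person's recruitment until the study completes, and at that point sends everyone the post-study survey.

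**Analysis.** Primary Analysis compares proportions over the study by χ² or t-test. Secondary and Ancillary Analysis compares the proportions with an event at least once during the study, and the average days of absence per participant. Neither section mentions length of observation.

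**The concern.** Access that starts on an individual date and has a length set by registration date implies a shared end date. The text on data collection has the same structure for both arms: an individual start, and an end when the study completes. If that is what is meant, a person who registers three months late contributes 9 months to an outcome described as a 12-month one.

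Two things would be at stake. First, the reported 12-month proportion would be a mixture over windows of 9 to 12 months. So would the at-least-once proportions and the days of absence. None of these would be well defined as written. Second, if uptake of a plan accumulates over time, shorter windows lower the rates in both arms and the difference expected between them, in a trial that has little power to spare.

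The problem would be hard to repair afterwards. Table 1 collects the primary outcome only at baseline and completion. A common-window result could not be recovered unless the final survey also asked when the plan was obtained or updated.

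**Working it through.** **1. The plan's own figure.** Inputs from Sample Size: 14.4% versus 29.4%, "5% level of significance, 80% power (2-sided test"), "at least 300 participants with 150 in each arm is needed", dropout about 25%.

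The pooled-variance formula for two proportions, without continuity correction, gives 119 per arm. 119 × 1.25 = 148.75, so 149 per arm and 298 in total, which matches the stated 300. (Dividing by 0.75 would give 159 per arm, 318 in total; that is a separate matter.)

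Evaluable per arm: 150 × 0.75 = 112.5. With p̄ the mean of the two rates,

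power = Φ{ [ |p₂ − p₁|√n − 1.96√(2p̄(1 − p̄)) ] / √(p₁(1 − p₁) + p₂(1 − p₂)) }

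For 0.144 and 0.294, p̄ = 0.219 and the expression is Φ{(1.591 − 1.146)/0.575} = Φ(0.773) = 78.0%. This is the 12-month reference.

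**2. Assumptions for the illustration.** The article gives neither an accrual pattern nor the timing of plan uptake. I assume that the planning rates are 12-month cumulative rates, that the hazard is constant, and that the windows are alike in both arms. With t in years, p(t) = 1 − (1 − p)^t.

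**3. Everyone observed for 9 months (t = 0.75).**
- Control: 1 − 0.856^0.75 = 11.0%
- Intervention: 1 − 0.706^0.75 = 23.0%
- Difference 12.0 points, power 66.9%

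**4. Entry uniform, so windows uniform on 9 to 12 months.** The average of p(t) over t from 0.75 to 1 is 1 − [(1 − p) − (1 − p)^0.75] / [0.25 ln(1 − p)].
- Control 12.7%, intervention 26.2%
- Difference 13.5 points, power 72.9%

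**5. Sensitivity to the time course.** With rates proportional to time:
- Uniform entry: 12.6% versus 25.7%, difference 13.1 points, power 70.8%
- All at 9 months: 10.8% versus 22.1%, difference 11.3 points, power 62.6%

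**6. The other reading: the outcome window stays at 12 months and only access is shortened.** Let h₁ = −ln 0.856 = 0.1555 and h₂ = −ln 0.706 = 0.3481, with the extra hazard acting only during access. The intervention rate is 1 − exp{−[h₁ + (h₂ − h₁)t]}, and control stays at 14.4%.
- Access of 10.5 months: 27.7%, power 68.8%
- Access of 9 months: 25.9%, power 57.7%

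**7. Individual 12-month access and window for all.** 14.4% versus 29.4%, power 78.0%, no loss.

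**The case against.** The strongest reply is that the 9-to-12-month range appears once, under an intervention heading, and describes access to Healthy.me. A reader might infer that the protocol sets follow-up at 9 to 12 months; no sentence says so. The beginning of the study in Table 2 can mean each participant's own start, which fits the section that puts everyone's final survey at 12 months. That stands: unequal outcome windows are an inference. The inference is still well supported by Study Procedure, which ends data collection for both arms when the study completes.

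The second reply concerns the numbers. The 14.4% is a survey prevalence of possessing a plan, and Table 1 records the primary outcome as having one. A prevalence need not shrink because observation is three months shorter. That stands too. One cannot say that late registrants would miss the planning rates, and the power figures are conditional.

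Third, a reader might infer bias between the arms. The arms run concurrently and allocation is in permuted blocks, so windows should balance and the comparison stays valid. The same holds for season.

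Fourth, it would be wrong to say that the detectable difference gets worse. At 112.5 per arm and 80% power, the same formula gives 15.4 points at a base rate of 14.4%, 14.9 at 12.7% and 14.3 at 11.0%. It is the expected difference, and with it power, that falls.

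Finally, moving the primary outcome to month 9 is a tempting remedy. It has the lowest power under a common close (67%, or 63% with rates proportional to time) and needs a measurement that Table 1 does not collect.

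**Conclusion.** The contradiction on length of access is on the page and must be reconciled. A common closing date, with windows of 9 to 12 months in both arms, is the natural reading of the data-collection text but is not stated.

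Under that reading the 12-month outcome is not well defined as written. The illustrative cost is a fall in the expected difference from 15.0 to about 13.1–13.5 points and in power from 78% to about 71–73% with uniform entry. If everyone were at 9 months, these would be 11.3–12.0 points and 63–67%. These figures rest on treating the planning rates as 12-month cumulative rates and on an assumed time course and accrual; the documents fix none of these. Keeping a 12-month outcome window with shortened access is no safer on comparable assumptions (58–69%).

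The harm is to interpretation and power. There is no evident bias. It is worth correcting because the remedy is cheap and the data cannot easily be repaired later.

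**What to change.** Time the outcome window and the automated post-study survey from each participant's own randomisation date, with the same 12-month window for everyone in both arms. State this in Outcome Measures and in Table 2, so that the beginning of the study has one meaning, and align the Study Procedure wording on when surveys end. Reconcile the statements on length of access in the Abstract, Participants, Intervention Group and Exposure, and Control with that window.

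The cost is a scheduling rule in the survey tool and a wording amendment. The last data would arrive up to about 3 months later than with a common closing date.
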